## Abstract

**Background:**

It has been shown that intracranial artery stenosis (ICAS) plays a key role in Chinese ischemic stroke or transient ischemic attack (TIA) patients. Many vascular diseases can lead to ICAS, such as atherosclerosis, dissection, vasculitis, moyamoya disease, and reversible cerebral vasoconstriction syndrome (RCVS). In addition, progression of intracranial atherosclerotic disease (ICAD) will increase the risk of ischemic cerebrovascular events. The ICASMAP study primarily aims to determine the etiology and disease distribution of ICAS using noninvasive magnetic resonance (MR) imaging and evaluate the rate for progression of ICAD in symptomatic population.

**Methods:**

The ICASMAP study is a prospective, observational, and multicenter study by recruiting 300 subjects (18–80 years old) with recent stroke or TIA (within 2 weeks after onset of symptoms) in China. All the subjects will undergo MR imaging examination including brain and intracranial artery MR imaging at baseline. In addition, the clinical risk factors will be collected and blood biomarkers will be tested. A subgroup of more than 200 subjects who were diagnosed with ICAD according to baseline MR imaging will be followed up for 2 years. During the follow‐up study, MR imaging examination will be performed at 12 and 24 months. The primary end point is presence of progression of intracranial artery atherosclerotic plaques.

**Conclusions:**

The ICASMAP study investigates the etiology of ICAS and progression of ICAD in Chinese stroke patients and may help to improve the precise diagnosis and intervention of ICAS and stroke prevention.

## INTRODUCTION

1

Stroke is the second most common cause of death worldwide (Group GBDNDC, 2017; Truelsen et al., 2015) and has become the leading cause of death in China (Wang et al., 2017). Previous studies demonstrated that intracranial artery stenosis (ICAS) is significantly associated with ischemic stroke, particularly in Chinese population. A study (Wang et al., 2014) reported that 46.6% of Chinese patients with ischemic stroke had severe intracranial artery stenosis (stenosis > 50%). Although most of stenotic diseases in intracranial arteries are atherosclerotic (Hart et al., 2014), a substantial number of other vascular diseases, such as dissection, arteritis, moyamoya disease, and reversible cerebral vasoconstriction syndrome (RCVS), can also lead to intracranial artery luminal narrowing (Obusez et al., 2014; Sikkema et al., 2014; Yuan et al., 2015). Therefore, accurate diagnosis of the etiology of ICAS is important to personalize treatment strategies.

It has been shown that the progression of intracranial atherosclerotic disease (ICAD) will subsequently increase the risk of ischemic cerebrovascular events (Arenillas et al., 2001; Wong, Li, Lam, Chan, & Kay, 2002). Previous studies have shown that baseline symptomatic ICAD (Ryu et al., 2014), diabetes (Miyazawa, Akiyama, & Yamagata, 2007), smoking (Miyazawa et al., 2007), and treatment of statin (Kim, Kim, Kwon, Kim, & Kang, 2012) and cilostazol (Kwon et al., 2005) were associated with ICAS progression. Shimizu et al. (2013) summarized the inflammatory biomarkers associated with progression of ICAS, such as interleukin‐6, interleukin‐18, C‐reactive protein, intercellular adhesion molecule 1, and E‐selectin. However, the progression of ICAD may not be parallel to the changes of luminal stenosis. Currently, the risk factors for ICAD progression determined by metrics beyond luminal stenosis, such as plaque size and plaque compositions, remain unclear. Investigation of the risk factors of ICAD progression will be helpful for stabilizing ICAD and stroke prevention.

Magnetic resonance (MR) vessel wall imaging is capable of accurately evaluate vascular diseases that lead to ICAS according to the features of location, shape, signal pattern, remodeling, and contrast enhancement of lesions (Choi, Jung, & Lee, 2015; Mossa‐Basha et al., 2015). However, the results of recent studies on distribution of etiology of symptomatic ICAS are controversial. A MR vessel wall imaging study by Ahn et al. (2015) showed that moyamoya disease was the most dominant etiology of unilateral middle cerebral artery (MCA) stenosis in South Korean young adult patients with none or one atherosclerosis risk factor, followed by atherosclerosis, dissection, and vasculitis. However, a recent MR vessel wall imaging study reported that the most common etiology of ICAS in Chinese young patients with unilateral middle cerebral artery stenosis was ICAD (Xu et al., 2017). In addition, investigators have proved that MR vessel wall imaging is a reproducible technique (Qiao, Anwar et al., 2016; Qiao, Guallar et al., 2016), which can be reliably utilized to monitor the changes of ICAD during natural follow‐up or medical treatment.

In this article, we show the rationale and design of ICASMAP (Intracranial Artery Stenosis MR imaging: Aetiology and Progression) study. ICASMAP is a prospective, observational, multicenter study that aimed to investigate the etiology of symptomatic ICAS and the progression of ICAD using MR vessel wall imaging. The initiation of this study will improve the accuracy of diagnosis and intervention of ICAS and stroke prevention.

Therefore, the primary objectives of ICASMAP study are as follows: (a) to determine the etiology and disease distribution of ICAS using MR vessel wall imaging in symptomatic patients and (b) to evaluate the rate for progression of ICAD during 2‐year follow‐up. The secondary objective was to investigate risk factors for progression of ICAD.

## METHODS

2

### Study design and population

2.1

The ICASMAP study (NCT03417063) is a prospective, observational, and multicenter study. This study planned to recruit 300 patients (age range: 18–80 years old) who had recent ischemic stroke or transient ischemic attack (TIA; within 2 weeks after onset of symptoms) and ICAS (stenosis range from 30% to 99% that is the responsible lesion for symptoms) in at least one vascular bed determined by computed tomography angiography (CTA) or MR angiography. The ICAS lesions can be located in intracranial internal carotid artery, basilar artery, intracranial segment of vertebral artery (V4), M1 segment of middle cerebral artery, A1 segment of anterior cerebral artery, or P1 segment of posterior cerebral artery. The patients will be recruited from 18 different hospitals across Beijing–Tianjin–Hebei region in China. The exclusion criteria include the following: (a) severe carotid artery atherosclerotic disease (stenosis ≥ 70%); (b) cardiogenic thrombosis; (c) heart failure or respiratory failure; (d) renal dysfunction (serum creatinine ˃133 μmol/L); (e) serious disturbance of consciousness; (f) cerebral neoplasms; (g) intracranial hemorrhage; (h) claustrophobia; (i) contraindications to MRI; and (j) pregnant or plan to pregnant within recent 2 years. All subjects will undergo brain and intracranial artery MR imaging. For subjects who were diagnosed with ICAD (*n* > 200), the clinical follow‐up will be conducted at 3, 6, 12, and 24 months and the MR imaging follow‐up will be performed at 12 and 24 months, respectively. Previous studies reported that the progression rate of ICAS was 3.86% per year (Ryu et al., 2014) and the intra‐reader and inter‐scan variation in measuring maximum wall thickness of intracranial plaques was 6.67% (Zhang et al., 2018). Therefore, it might be reasonable to detect the 2 years’ progression of intracranial atherosclerosis disease (7.72%) which is greater than the variation of quantitative measurement by MRI. A flow chart of the study procedures is presented in Figure 1. The study protocol was approved by local Institutional Review Board, and all patients provide written informed consent.

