### Sample size estimation

2.7

According to previous studies, we assume about 20% of participants may have progression of intracranial atherosclerotic plaque in 2 years (Arenillas et al., 2008; Kwon et al., 2005; Ryu et al., 2014). Thus, 300 subjects are needed to estimate the progression rate of intracranial atherosclerotic plaque with a margin of error of 0.25× progression rate and a lost to follow‐up rate of 15%.

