### Statistical analysis plan

2.9

The continuous variables will be presented with mean ± standard deviation, and the categorical variables will be described as percentage. The prevalence of different vascular diseases, such as atherosclerosis, dissection, arteritis, moyamoya disease, and RCVS, that lead to ICAS in different age groups (<40, 40–50, 50–60, 60–70, and >70 years) will be calculated. The morphological measurements, T1 hyperintensity, enhancement patterns, and remodeling will be compared among different arterial diseases using One‐Way ANOVA or Mann–Whitney U test when appropriate. The progression rate of ICAD was calculated. Spearman correlation will be analyzed to determine the association of plaque features at baseline, clinical risk factors and blood biomarkers with progression of ICAD. Logistic regression model will be performed to calculate the odds ratio (OR) and corresponding confidence interval (CI) of plaque features at baseline, clinical risk factors and blood biomarkers in discriminating progression of ICAD before and after adjusting for confounding factors. Cox regression will be analyzed to calculate the hazard ratio and corresponding 95% CI of baseline intracranial artery vessel wall MR features in predicting for the cerebrovascular events. The intraclass correlation coefficient (ICC) and Kappa value were calculated for continuous and categorical variables in intra‐reader and inter‐reader reproducibility studies, respectively. All statistical analyses will be performed using SPSS 16.0 (SPSS Inc., Chicago, IL) and SAS (SAS Inc., North Carolina, NC).

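### The detectability argument in section 2.1 compares two different quantities, and the 0.25× margin in section 2.7 is not assured in the ICAD patients who are actually followed

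*Protocol article*

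**What the plan says.** **Detectability (section 2.1, Study design and population).** The article cites earlier work in which "the progression rate of ICAS was 3.86% per year". For repeat readings and repeat scans it cites a study whose "variation in measuring maximum wall thickness of intracranial plaques was 6.67"%. It doubles the first figure and, in hedged terms, considers it feasible to detect 2-year "progression of intracranial atherosclerosis disease (7.72%) which is greater than the variation of quantitative measurement by MRI".

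**Sample size (section 2.7).** Here "we assume about 20% of participants may have progression of intracranial atherosclerotic plaque in 2 years". The study cited for the 3.86% is one of the three given in support. The section concludes that "300 subjects are needed to estimate the progression rate of intracranial atherosclerotic plaque". The precision target is a "margin of error of 0.25× progression rate", and 15% of patients are expected to be lost. It states no confidence level for the margin.

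**Who is followed (sections 2.1 and 2.4).** All 300 have baseline MR imaging, but follow-up imaging at 12 and 24 months is only for those diagnosed with ICAD, given as more than 200.

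**End point (section 2.6).** Progression is met by any one of four criteria at 1 or 2 years: a rise of at least 10% in maximum wall thickness, a higher stenosis grade, new T1 hyperintensity, or a higher enhancement grade.

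**The concern.** The progression rate is a primary objective and progression is the primary end point, so two things have to be right: the argument that MR imaging can detect progression, and the precision claimed for its rate.

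The first rests, as far as numbers go, on 7.72% being larger than 6.67%. One is a rate of disease progression and the other an error in measuring wall thickness. Their order carries no information about whether a patient classed as a progressor has truly progressed.

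The second is a relative margin, which depends strongly on the assumed rate and on how many patients contribute. The article carries two 2-year figures, 7.72% and 20%, with no bridge between them. It also attaches the margin to 300 patients although fewer may have follow-up imaging. A reader would expect a tighter estimate than the design may deliver.

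**Working it through.** **1. What is being compared**

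- *If 3.86% per year is a share of patients:* 7.72% counts people and 6.67% is an error in one person's wall thickness. They cannot be ranked. The article leans towards this reading. Section 2.7 uses the term progression rate for a share of participants, and the Discussion describes the source of the 3.86% as comparing the risk of stenosis progression between symptomatic and asymptomatic subjects.
- *If it is a mean change:* the Discussion indicates that the source measured stenosis, whereas 6.67% concerns wall thickness. The quantities still differ.

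**2. The comparison that would bear on detectability**

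This is the individual 10% thickness cut-off against the error of a change. The article does not define the 6.67%, so two assumptions are shown, each with normal errors and a truly stable plaque at one follow-up:

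- 6.67% is already the SD of a change: P(apparent rise ≥ 10%) = 1 − Φ(10/6.67) ≈ 7%.
- 6.67% is the SD of one measurement: SD of change = √2 × 6.67 = 9.43%, and 1 − Φ(10/9.43) ≈ 14%.

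These are illustrations only, but they are not negligible beside a planned rate of 7.72% or 20%.

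**3. Reproducing the 300**

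Inputs from section 2.7: p = 0.20, margin d = 0.25 × 0.20 = 0.05, loss 15%. Confidence is assumed to be 95%, the level section 2.9 names for the Cox analysis ("hazard ratio and corresponding 95% CI of baseline intracranial artery vessel wall MR features").

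- n = 1.96² × p(1 − p)/d² = 3.8416 × 0.16/0.0025 = 245.9, so 246 evaluable.
- 246/0.85 = 289.4, so 290 followed.

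This is 10 below the stated 300 and fits rounding up. With 300 followed, 255 are evaluable and the half-width is 1.96 × √(0.16/255) = 4.91 points (0.245×), inside the target. At 90% confidence the same formula gives 174 evaluable and 205 followed, much further from 300, so 95% is the more plausible level.

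**4. Precision in the patients who are followed**

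Half-width = 1.96 × √(p(1 − p)/N), with N = followed × 0.85. The 250 row is an illustrative midpoint.

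| ICAD followed | Evaluable N | p = 20% | p = 7.72% |
|---|---|---|---|
| 200 (floor) | 170 | ±6.0 points (0.30×) | ±4.0 points (0.52×) |
| 250 | 212 | ±5.4 points (0.27×) | ±3.6 points (0.47×) |
| 300 (all have ICAD) | 255 | ±4.9 points (0.25×) | ±3.3 points (0.42×) |

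At 20% the margin holds only with about 290 followed, that is, if 290/300 = 97% of recruits have ICAD.

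**5. What the 0.25× margin would need at 7.72%**

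n = 3.8416 × 0.9228/(0.0625 × 0.0772) = 734.7, so 735 evaluable, and 735/0.85 = 864.7, so 865 followed. This applies only if 7.72% is a share of patients and is the right rate for this end point.

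**The case against.** Several counter-arguments have force.

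- *Detectability does not rest on that one sentence.* The Introduction cites studies of the reproducibility of vessel wall imaging, section 2.8 plans a reproducibility study, and the 10% cut-off exceeds 6.67%. This stands: the comparison is the only numerical argument for detectability, not the only argument. It does not make the comparison valid.
- *The two rates may describe different things.* The 3.86% comes from a study of stenosis in symptomatic and asymptomatic subjects. The 20% is for a four-criterion end point in a symptomatic cohort and rests on three sources. A higher figure is to be expected, and this may explain part of the 2.6-fold gap (20/7.72). The article does not say so, which leaves a missing bridge rather than a proven contradiction.
- *On a mean-change reading the conflict disappears.* This is correct. The 735 and 865 figures disappear with it. A reader might also infer that 7.72% is undetectable because it lies below the 10% cut-off or below 9.43%. The article does not support that. A group mean may lie below an individual cut-off while some patients cross it, and a mean is judged against its standard error (9.43/√170 = 0.72 points for measurement error alone). The 9.43% itself assumes that 6.67% is a single-measurement SD.
- *The sample size uses 20% only, and the follow-up group is given as more than 200.* Both are true. The 170 is therefore a floor and not a forecast.

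**Conclusion.** The comparison of 7.72% with 6.67% does not show that progression can be detected, whichever way the 3.86% is read. If the 3.86% is a share of patients, as the article's own usage suggests, 7.72% is also unreconciled with the 20%.

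The stated 0.25× margin is not assured in the patients followed. At 20% it needs about 290 followed. At the subgroup floor of 200 with 15% loss the half-width is ±6.0 points (0.30×), and it would be ±4.0 points (0.52×) at 7.72%. These figures assume 95% confidence and a normal-approximation interval. The confidence assumption matters: at 90%, 170 evaluable at a rate of 20% would give 1.645 × √(0.16/170) = 5.0 points, practically the stated margin, but the 300 would then be hard to explain.

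A reader might conclude that 300 is wrong or that 865 patients are needed. The article does not support either. The 300 is adequate at 20% if all 300 are followed, and 7.72% enters no sample-size calculation. The shortfall at 20% is modest. The point concerns an invalid argument and a precision claim attached to the wrong group.

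**What to change.** 1. In section 2.1, delete the comparison of 7.72% with 6.67%. Alternatively, replace it with the 10% individual cut-off set against the repeatability of change, saying whether 6.67% refers to one measurement or to a difference.
2. State what the 3.86% per year measures (share of patients or mean change, stenosis or wall thickness).
3. In section 2.7, justify one planning rate for the four-criterion end point and explain how it relates to the cited stenosis figure.
4. Replace the single 0.25× claim with absolute half-widths for the ICAD patients expected to be followed, naming the confidence level. Keep the planning rate as the base case and show lower rates as a sensitivity range. With 170 evaluable this runs from ±6.0 points at 20% to ±4.0 points at 7.72%.

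The cost is a few sentences and a small table. No extra patients, visits or scans are needed. The one drawback is that the stated precision becomes slightly less favourable.

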**Figure 1 brb31154-fig-0001:**
[figure not shown]
Flow chart for study procedures of ICASMAP. ICAS, intracranial artery stenosis; MR, magnetic resonance; T1W, T1‐weighted; T2W, T2‐weighted; FLAIR, T2‐fluid‐attenuated inversion recovery; T2*W, T2*‐weighted; DWI, diffusion‐weighted image; 3D‐TOF, three‐dimensional time‐of‐flight; T1‐VISTA, T1 volumetric isotropic turbo spin echo acquisition; T1‐SPACE, T1 sampling perfection with application‐optimized contrast using different flip angle evolutions

### Clinical data collection

2.2

Each patient will undergo clinical visit at admission to hospital, discharge from hospital, 3, 12, and 24 months and telephone interview at 6 months. During each visit, demographic and clinical information (age, gender, body mass index [BMI], smoking, diabetes, hypertension, hyperlipidemia, use of antihypertensive, hypoglycemic drugs, lipid‐lowering drugs, anticoagulants, and antiplatelet drugs) and clinical events (new stroke [ischemic and hemorrhage], TIA, cerebrovascular recanalization, or death) will be recorded. The information of the history of smoking, the recent smoking and former smoking is recorded. Diabetes is diagnosed by demonstrating any one of the following conditions: fasting blood sugar level ≥126 mg/dl; 2‐hr oral glucose tolerance test result ≥200 mg/dl; or hemoglobin A1c ≥6.5%. Hypertension is defined as diastolic blood pressure ≥90 mmHg or systolic blood pressure ≥140 mmHg. The levels of lipoprotein including high‐density lipoprotein, low‐density lipoprotein, total cholesterol and triglycerides are recorded. Hyperlipidemia means elevated concentrations of any or all of the following lipids in the plasma: low‐density lipoprotein >140 mg/dl; total cholesterol >200 mg/dl; or triglycerides >150 mg/dl.

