### Blood biomarker test

2.3

The blood draw will be conducted at median cubital vein at admission to hospital, 3 and 12 months. The blood biomarkers including fasting glucose, hemoglobin, cholesterol level, homocysteine, serum uric acid, high‐sensitivity C‐reactive protein, intercellular adhesion molecule 1, E‐selectin, matrix metallopeptidase 9, plasminogen activator inhibitor‐1, lipoprotein (a), interleukin‐6, interleukin‐18, macrophage chemoattractant protein‐1, oxidized low‐density lipoprotein, and lipoprotein‐associated phospholipase A2 will be tested.

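### Hypertension, diabetes and hyperlipidemia are defined by measured thresholds alone, so patients with known disease controlled on treatment enter the risk-factor models as unexposed

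*Protocol article*

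**What the plan says.** Section 2.2 (Clinical data collection) gives three exposure definitions:

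- Hypertension: "Hypertension is defined as diastolic blood pressure ≥90 mmHg or systolic blood pressure ≥140 mmHg".
- Diabetes: "Diabetes is diagnosed by demonstrating any one of the following conditions", followed by cut-offs for fasting glucose, the 2-hour glucose tolerance test and hemoglobin A1c.
- Hyperlipidemia: "Hyperlipidemia means elevated concentrations of any or all of the following lipids in the plasma", followed by cut-offs for low-density lipoprotein, total cholesterol and triglycerides.

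None has an arm for a previous diagnosis or for current treatment. The same section separately records "use of antihypertensive, hypoglycemic drugs, lipid‐lowering drugs, anticoagulants, and antiplatelet drugs". Section 2.9 (Statistical analysis plan) puts the clinical risk factors into Spearman correlations and into logistic models that estimate odds ratios for "clinical risk factors and blood biomarkers in discriminating progression of ICAD before and after adjusting for confounding factors". The confounders are not named, and nothing says that drug use changes how a condition is coded.

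**The concern.** Read as written, a patient with hypertension whose pressure is below both cut-offs on treatment is coded as not hypertensive. The same holds for a treated diabetic patient with values below every limit, and for a patient whose lipids are controlled by a lipid-lowering drug. The reference group then contains both people who never had the condition and people who have it under control.

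Two things follow. The odds ratio answers a different question from the one a reader would take from the label: it contrasts currently raised values with everything else. And whether a diseased patient is coded as exposed depends on treatment, so disease and treatment are mixed in one variable. The introduction and discussion name diabetes and statin treatment among the factors linked to progression, so these are variables on which the secondary objective turns.

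**Working it through.** **The plan's own figure.** The article gives no calculation for this point. Only the anticipated progression of about 20% at 2 years (section 2.7) serves as an anchor. Everything else below is assumed.

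**Illustration 1: controlled patients keep the full excess risk.**

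Assumed: true prevalence of the condition E = 0.60, progression in the truly unexposed p0 = 0.14, true odds ratio 2.0, and a share f = 30% or 50% of those with the condition below threshold on treatment.

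- Odds in the unexposed: 0.14/0.86 = 0.1628. Doubled: 0.3256. So p1 = 0.3256/1.3256 = 0.2456.
- Overall progression: 0.6 × 0.2456 + 0.4 × 0.14 = 0.203, in line with the 20% in section 2.7.
- Risk in those coded unexposed: [(1 − E)·p0 + E·f·p1] / [(1 − E) + E·f].
  - f = 0.30: (0.056 + 0.18 × 0.2456)/0.58 = 0.1728. Observed odds ratio = 0.3256/0.2089 = **1.56**.
  - f = 0.50: (0.056 + 0.30 × 0.2456)/0.70 = 0.1853. Observed odds ratio = 0.3256/0.2274 = **1.43**.

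**Illustration 2: the retained risk is varied.**

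Assumed: E = 0.50, f = 0.40, overall progression fixed at 20%, and an odds ratio of 2.0 for uncontrolled disease against never having it. Solving 0.5·p0 + 0.5·p1 = 0.20 with an odds ratio of 2.0 gives p0 = 0.1457 and p1 = 0.2543. Controlled patients have risk p0 + g(p1 − p0), where g is the share of the excess that they keep. Group risks are held at these values as g changes.

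| g | Odds ratio, measured-value definition | Odds ratio, definition adding history or treatment |
|---|---|---|
| 1 | 1.59 | 2.00 |
| 0.5 | 1.77 | 1.78 |
| 0 | 2.00 | 1.57 |

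For g = 1, the coded-unexposed risk is (0.5 × 0.1457 + 0.2 × 0.2543)/0.7 = 0.1767, and the odds ratio is (0.2543/0.7457)/(0.1767/0.8233) = 1.59.

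**Wider range at g = 1.** Over prevalence 30–70% and f = 20–60%, a true odds ratio of 2 is seen as 1.87 down to 1.29, and a true odds ratio of 3 as 2.67 down to 1.44.

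The miscoding follows from the text alone. Its effect on the odds ratio depends on g, which the document does not give.

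**The case against.** **Attenuation is not certain.** A reader might infer that the risk-factor odds ratios are necessarily biased toward 1. The document does not support that. Attenuation requires controlled patients to keep excess risk. If they keep none, the measured-value odds ratio is not attenuated and the broader definition gives the lower figure (1.57 in illustration 2). The discussion itself reports that statin therapy may inhibit progression, so full retained risk cannot be taken for granted, least of all for lipids. This objection stands and makes the direction conditional. It does not make the measured-value definition a definition of disease.

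**Diabetes is not shown to rest on fasting glucose alone.** Section 2.3 says "The blood biomarkers including fasting glucose, hemoglobin, cholesterol level, homocysteine" and continues without naming hemoglobin A1c or a glucose tolerance test. But that list is open-ended. It also leaves out triglycerides, which section 2.2 records, and serum creatinine, which an exclusion criterion in section 2.1 needs. Absence from the list does not show that a test is not done, and the diabetes wording could admit earlier results. Only a request for clarification remains.

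**A single transient post-stroke reading is not stated.** A reader might infer that one raised value soon after the event counts as hypertension. The article gives no number of readings and does not say which visit fixes the status, so no false-positive rate can be derived from it.

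**The data permit repair.** Drug classes are recorded at each visit and lipid levels are kept as values, so nothing is irretrievably lost. That is correct and limits the severity. But adding drug use as a covariate does not by itself correct the coding of the condition, and the stated rule is the one an analyst would apply.

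**Conclusion.** The point holds in limited form. The stated definitions do not capture disease status: controlled patients are coded as unexposed, and the resulting odds ratios describe currently raised values with treatment mixed in. If controlled patients keep their excess risk, an odds ratio of 2.0 would be seen as about 1.4 to 1.6 under the central assumptions; if they keep little of it, the direction differs. Prevalence, the true odds ratio, the controlled share and the retained risk are all assumptions, so these figures illustrate and do not estimate.

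The consequence is confined to the secondary objective on risk factors for progression. The etiology distribution, the progression rate and the primary end point do not use these definitions. It is a stated rule that should be changed, not a detail left to a fuller document.

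**What to change.** For the analysis, code each condition at baseline as present if any of these applies: a documented prior diagnosis, current use of the corresponding drug class, or the measured threshold already in section 2.2. Keep drug use and the measured level as separate variables, so that disease, treatment and control can be told apart. This matters because the combined category alone would pool controlled and uncontrolled patients, and illustration 2 shows that pooling can itself lower the odds ratio.

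The cost is small: one history item on the case report form, some recoding, and a sentence in the analysis plan. Drug use is already collected.

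As a clarification only, reconcile the hemoglobin A1c and glucose tolerance criteria in section 2.2 with the test list in section 2.3.
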